## Abstract

**Background:**

Available evidence on the conservative treatment of knee osteoarthritis still leaves questions about the efficacy of platelet-rich plasma (PRP) and whether stromal vascular fraction (SVF) offers a superior therapeutic tool.

**Objective:**

This study aims to assess the clinical efficacy of SVF as adjuvant therapy to PRP on functionality and tissue regeneration for knee osteoarthritis.

**Methods:**

In a multicenter, randomized, triple-blind, controlled trial, 108 individuals with knee osteoarthritis will be block-randomized in a 1:1 ratio. Patients will receive an initial single PRP or PRP + SVF injection followed by PRP doses at 1 month and 2 months. The primary endpoint is functional improvement measured with the Western Ontario and McMaster Universities Osteoarthritis Index (WOMAC) at the 6-month follow-up. Secondary endpoints, collected at the 1-month, 2-month, 3-month, 6-month, and 12-month follow-ups, will include the pain visual analogue scale during maximal physical activity, WOMAC score, length of time to return to work and sports in days, magnetic resonance imaging (MRI)–based Whole-Organ Magnetic Resonance Imaging Score (WORMS), Magnetic Resonance Observation of Cartilage Repair Tissue (MOCART) score, MRI Area Measurement and Depth and Underlying Structures (AMADEUS) score at 6 months and at 12 months, adverse events, and serious adverse events.

**Results:**

Participant recruitment and data collection are expected to begin in July 2025 and finish in July 2027. Final end points will be gathered in August 2027, and the results are expected to be published in late 2027.

**Conclusions:**

The study results will provide insight into the clinical efficacy of SVF as adjuvant therapy to PRP on functionality and tissue regeneration in patients with knee osteoarthritis.

**Trial Registration:**

ClinicalTrials.gov (NCT05660824); https://clinicaltrials.gov/study/NCT05660824

**International Registered Report Identifier (IRRID):**

PRR1-10.2196/62659

## Introduction

Osteoarthritis, the most common joint disease [1], has a high social and individual impact, and the development of therapeutic options is a public health priority. Its multifactorial etiology is still a source of active research [2,3]. The most common conservative treatments for osteoarthritis include painkillers, active physical therapies, orthotics, corticosteroid infiltrations, hyaluronic acid, and platelet-rich plasma (PRP) [1,4].

PRP may be beneficial in osteoarthritis by interfering with catabolic and inflammatory events and by subsequently promoting anabolic responses. Activation of PRP releases biologically active components, including platelet-derived growth factor, transforming growth factor-β, type I insulin-like growth factor, and vascular endothelial growth factor. These proteins are responsible for a range of critical tissue healing roles, such as chondrocyte and mesenchymal stem cell (MSC) proliferation, bone and vessel remodeling, inflammatory modulation, and collagen synthesis [5].

Several clinical trials have found improvement in clinical outcomes for osteoarthritis [6,7], presumably associated with the chondroprotective effect of PRP. Nevertheless, despite the numerous studies on the subject, the evidence is inconsistent, there is a lack of uniform improvement in functional outcomes, and an in vivo effect on human cartilage regeneration has not yet been demonstrated [8,9].

Stem cell therapy has arisen as a new therapeutic option for knee osteoarthritis. Preclinical models have elucidated how injected adipose-derived mesenchymal stem cells (AD-MSCs) coordinate the cartilage regeneration process [10-12] through paracrine mechanisms [13], producing cytokines and trophic bioactive factors that stimulate cellular proliferation and reduce inflammation, fibrosis, oxidative stress, and chondrocyte senescence [1].

AD-MSCs seem to have a better hypoxic tolerance, fewer immunologic and inflammatory responses [14], better chondrogenic induction and gene expression [15], and less variable and more reliable clinical result [14] than bone marrow–derived mesenchymal stem cells (B-MSC).

Stromal vascular fraction (SVF), a product from processed adipose tissue, contains MSCs, endothelial precursor cells, T regulatory cells, macrophages, smooth muscle cells, pericytes, and preadipocytes. SVF extraction and injection techniques have recently been used as an alternative to harvest AD-MSCs due to their logistical simplicity and feasibility in clinical practice. The superiority or inferiority of SVF compared with AD-MSC has not yet been established.

Randomized trials indicate that intra-articular SVF injections can provide clinical benefits in knee osteoarthritis [16], with some studies noting cartilage quality improvements [16-19]. Despite their potential, SVF treatments are invasive, costly, and supported by a limited number of studies, many of which lack the homogeneity needed for clinical guideline endorsement, even though research in this area is steadily increasing and yielding promising results. Although PRP is often recommended in sports medicine for knee osteoarthritis, it is unclear whether combining it with SVF offers greater benefits for patients unresponsive to conservative treatment. This randomized controlled trial (RCT) will be the first to provide comparative data on the efficacy of SVF as an adjunct to PRP, addressing a critical gap in osteoarthritis treatment research.

The objectives of this study are to assess the clinical efficacy of SVF as adjuvant therapy to PRP on (1) functionality for knee osteoarthritis and (2) tissue regeneration for knee osteoarthritis.

## Methods

### Study Design

This multicenter, parallel-group, triple-blind study will enroll 108 patients who will be randomly assigned in a 1:1 ratio to either the intervention (SVF+PRP injection at baseline) or control group (PRP-only injection at baseline) using stratified randomization. The study will use a superiority framework.

The follow-up will last 12 months, with endpoints at 1 month, 2 months, 3 months, 6 months, and 12 months.

### Study Setting

In this multicenter study, we aim to recruit all patients between July 2025 and August 2027 in the Sports Medicine Division of La Providence Hospital and in the Rehabilitation division, Hôpital Fribourgeois, both in Switzerland. The lead center is the Sports Medicine Division of La Providence Hospital where author AS is the sponsor-investigator. All the interventions will be performed in the lead center.

### Eligibility Criteria

Patients will be recruited if they have knee osteoarthritis with persistent symptoms despite appropriate first-line treatment (ie, active physical therapies, sport and daily activity adaptations, orthotics use, medication) and for whom a surgical procedure is not indicated nor recommended.

The following main inclusion criteria will be used: (1) age older than 16 years; (2) symptomatic knee osteoarthritis confirmed by magnetic resonance imaging (MRI); (3) absence of free or displaced meniscal or cartilage fragments on the MRI of the affected knee; and (4) failure of first-line conservative management, including medical or infiltrative treatment, orthotics use, active rehabilitation plan, and adaptation of sports and work habits, in the last 3 months.

The following main exclusion criteria will be used: (1) patients familiar with the lipoaspiration process; (2) significant disease of the contralateral member with a disability, as evaluated with a Western Ontario and McMaster Universities Osteoarthritis Index (WOMAC) score >80%; (3) co-existence of microcrystalline disease (ie, gout, pseudogout); (4) active inflammatory rheumatic disorders; (5) a need for regular anti-inflammatory treatment (either nonsteroidal anti-inflammatory drugs [NSAIDs] or corticosteroids) or anticoagulants; (6) patients with decompensated renal failure, hepatic dysfunction, or severe pulmonary or cardiovascular disease; (7) patients with an immunocompromised status; and (8) women who are pregnant or intend to become pregnant during the study.

If bilateral disease is present and both sides require either the experimental or control intervention, only the most symptomatic side will be studied.

Informed consent will be obtained by the local site investigator. Other physicians in associated structures (ie, orthopedists, general practitioners, physiotherapists) are informed of the study and will be asked to refer patients to the referent sports medicine departments.

### Interventions

In both study groups, the intervention will be performed in the operating room under aseptic conditions and following the Arthrex protocols to prepare the autologous conditioned plasma [20], which is our PRP, and autologous conditioned adipose [21], which is our SVF, as described in the following paragraphs.

The patient is placed with a surgical drape hiding the interventional zone from the patient’s sight. The blinded investigator performs a 1.5 mm incision under local anesthesia on each abdomen side in order to introduce the microcannula used to extract the SVF. Tumescent solution is prepared by mixing 500 mL NACL with 30 cc 2% lidocaine + adrenaline 1:200000 and 3 cc 8.4% sodium bicarbonate, then 60 mL of this preparation are injected into each side and left in place. An interval of 20 minutes is allowed, which is necessary to let the tumescent solution act on the abdominal adipose tissue. At this point, the blinded investigator leaves the room. In the experimental arm, the unblinded investigator uses a double syringe system to extract 30 mL adipose tissue from the abdominal incisions. This is then centrifugated at 2500 rpm for 4 minutes. The oil and water are discarded. The lipoaspirate is then filtered using two 20 mL syringes and a 1.4-mm diameter transfer hub. One last centrifugation is performed at 2500 rpm for 4 minutes obtaining 2 mL to 6 mL SVF and the remaining oil. This last mixture is then discarded. In the control arm, the unblinded investigator performs a sham adipose tissue extraction by introducing the extraction cannula and moving it for 2 minutes on each side. In both study arms, the venipuncture is then performed, and 15 mL blood are extracted for the PRP preparation using the Arthrex double syringe system [20]. The blood is then centrifuged at 1500 rpm for 5 minutes, resulting in 4 mL to 7 mL of PRP. No anticoagulant, calcium chloride, nor other PRP activator is added. Following the aseptic technique, the unblinded investigator prepares the SVF-PRP mixture or PRP alone in an opaque 10-mL syringe. In parallel, the patient is prepared for the ultrasound-guided injection procedure. With an 18-gauge needle, the SVF-PRP mixture or PRP alone is then injected by the blinded investigator.

Postintervention care includes (1) partial weight-bearing for 1 month; (2) active strengthening of the muscles without overloading the knee using, if possible, the blood-flow restriction technique and gentle nonweight-bearing muscle activation, including core stability exercises; (3) mobility; and (4) modification of daily activities, work, and sports habits.

A total of 5 follow-up visits are planned for the study, during which principal and secondary outcomes will be gathered by a blinded investigator. At the 1-month and 2-month follow-up visits, patients in both study arms will receive 2 additional ultrasound-guided PRP injections performed by the blinded investigator and following the same Arthrex autologous conditioned plasma technique. The same postintervention care will be provided after these 2 PRP injections. Figure 1 shows the study flow chart.

Anticoagulants (eg, aspirin) and anti-inflammatory drugs (eg, ibuprofen, naproxen, meloxicam) should not be used 2 weeks before and 2 weeks after each injection as it can potentially interrupt the therapeutic acute inflammatory response and cytokine production.

Active physical therapies regimens, orthotics use, sports, and daily activities are adapted to the patient, on a day-by-day basis, during the postintervention care.

**Figure 1 figure1:**
[figure not shown]
Study flow chart. MRI: magnetic resonance imaging. PRP: platelet-rich plasma.

### Outcome Measurements and Assessments

The primary outcome is functional improvement measured with the 0%-100% normalized WOMAC at the 6-month follow-up, where 0% indicates complete absence of symptoms and 100% indicates maximal possible symptom severity. A clinically relevant functional improvement is a difference of 9.1 points out of 100 points.

The secondary outcomes will be clinical and radiological parameters gathered at the 1-month, 2-month, 3-month, 6-month, and 12-month follow-ups. These include a 10-point pain visual analogue scale (VAS) during maximal physical activity performed by the patient according to manageable pain and clinical recommendations, the 0%-100% normalized WOMAC [2], length of time to return to work and sports in days, adverse events (AEs), and serious adverse events (SAEs). Pain will be assessed as an AE of interest, during the intervention and 48 hours following the intervention.

The improvement in cartilage quality will be assessed at the 6-month and 12-month follow-ups (previous MRI should not be dated more than 3 months before the intervention) using 3 key MRI-based scoring systems: Area Measurement and Depth and Underlying Structures (AMADEUS) [13], Whole-Organ Magnetic Resonance Imaging Score (WORMS) [22], and Magnetic Resonance Observation of Cartilage Repair Tissue (MOCART) [23].

We initially planned to statistically assess these outcomes at 6 months and 12 months. However, assessment of these parameters at other time points might be subject to exploratory analysis.

The participant timeline is presented in Table 1. The following information will be collected at baseline: age, gender, height, weight, BMI, smoking status, comorbidities, baseline Kellgren–Lawrence grade, current and previous treatments, and posttraumatic etiology. The set of clinical and radiological scores include the VAS, WOMAC, return to work and sports in days, AMADEUS, WORMS, and MOCART.

**Table 1 table1:** Study assessments and procedures at the study visits.

Procedures	Screening^a^	Baseline	Visit 1	Visit 2	Visit 3	Visit 4	Visit 5
Timing (visit window)	–3 weeks (+3 weeks)	0	1 month (±7 days)	2 months (±7 days)	3 months (±7 days)	6 months (±7 days)	12 months (±7 days)
Informed consent	X	—^b^	—	—	—	—	—
Inclusion/exclusion criteria	X	—	—	—	—	—	—
Baseline characteristics	—	X	—	—	—	—	—
Clinical scores	—	X	X	X	X	X	X
MRI^c^	—	X	—	—	—	X	X
Randomization	—	X	—	—	—	—	—
Lipoharvesting or sham lipoharvesting	—	X	—	—	—	—	—
Intervention^d^	—	X	—	—	—	—	—
PRP^e^ injection	—	—	X	X	—	—	—
Concomitant medication	—	X	X	X	X	X	X
AEs^f^ and SAEs^g^	—	X	X	X	X	X	X

^a^Screening and baseline visits can be performed on the same day if the patient has been given reasonable time to make a consented decision about participation in the study.

^b^—: not applicable.

^c^MRI: magnetic resonance imaging.

^d^Stromal vascular fraction+platelet-rich plasma (PRP) or PRP-only injection depending on the group.

^e^PRP: platelet-rich plasma.

^f^AEs: adverse events.

^g^SAEs: serious adverse events.

### Sample Size

The sample size for this study was calculated using PS software (Vanderbilt University) [24]. We aimed to detect a clinically meaningful difference of 9.1% in the absolute change in the WOMAC function score between the experimental and control groups. The calculation assumed an SD of 13.9%, based on findings from the study conducted by Tubach et al [25].

In their study, Tubach et al [25] evaluated changes in the WOMAC function score in patients with knee osteoarthritis treated with NSAIDs over a 4-week period. They reported an average baseline WOMAC function score of 42.8 (SD 16.1) and an absolute improvement of –11.6 (SD 13.9). These values were used to estimate the variability in absolute changes for our calculation.

With these parameters, a sample size of 108 patients (54 per group) was determined to provide 90% power to detect the specified difference at a 5% significance level using a 2-tailed test. This calculation ensures that our study is adequately powered to detect a meaningful treatment effect based on absolute improvements in functional outcomes. The study will collaborate with health care providers in both study centers to achieve the target sample size. Additionally, potential participants will be contacted through patient registries and referrals. All recruitment efforts will comply with ethical guidelines and prioritize informed consent. Figure 2 shows the CONSORT (Consolidated Standards of Reporting Trials) diagram [26].

**Figure 2 figure2:**
[figure not shown]
CONSORT (Consolidated Standards of Reporting Trials) diagram showing the flow of participants through each stage of the randomized trial. PRP: platelet-rich plasma; SVF: stromal vascular fraction.

### Randomization and Blinding

Study participants will be randomized at a 1:1 ratio to either the intervention arm or the active comparator arm using a randomization table and blocked randomization with blocks of 4 patients. Participants will be assigned to specific strata based on age (older or younger than 40 years) and the presence of cartilage defects (partial, full, or full with bone deformation).

The unblinded investigator responsible for the study interventions will perform the randomization shortly before administering the interventions. This study is triple-blinded: (1) Participants will be unaware of their group assignment throughout the intervention and study duration, (2) the investigator performing the intraarticular injection and the outcome assessor will remain blinded, and (3) the statistician will also be blinded. The investigator responsible for preparing the PRP+SVF or PRP-only preparation will be unblinded and will not participate in outcome assessments.

All patients will undergo a venipuncture, either a lipoaspirate or a sham lipoaspirate, followed by an ultrasonographically guided PRP or PRP+SVF injection. It is anticipated that unblinding will not be required to ensure patient safety, as no known adverse effects of the SVF (such as local pain, tenderness, hematoma on donor site, or infection) require unblinding for clinical management. However, if unblinding becomes necessary due to unexpected circumstances, the unblinded investigator will disclose the allocated intervention for the affected patients.

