The meta-analysis by Lee et al [19] showed some differences between both therapies on clinical outcomes. A significant improvement in the VAS score was found at 6 months and 12 months with AD-MSCs (6 months: MD=–1.62, 95% CI –2.46 to –0.79; 12 months: MD=–1.97, 95% CI –3.22 to –0.72), whereas SVF showed significant results only at 12 months (6 months: MD=–2.32, 95% CI –5.15 to 0.52; 12 months: MD=–2.13, 95% CI –3.06 to –1.21). In contrast, functionality measured with WOMAC scores improved significantly 6 months after SVF treatment (MD=–6.12, 95% CI –10.71 to 1.52), while AD-MSC therapy yielded significant improvements only after 12 months (6 months: MD=–1.96, 95% CI –5.36 to 1.45). At 12 months and 24 months, both SVF and AD-MSC therapies produced significant improvements in the WOMAC score (12 months SVF: MD=–9.09, 95% CI –12.67 to –5.51; 12 months AD-MSC: MD=–9.19, 95% CI –12.48 to –5.90; 24 months SVF: MD=–10.71, 95% CI –18.49 to –2.93; 24 months AD-MSC: MD=–6.88, 95% CI –10.24 to –3.52).

The first main strength of our study design is the large sample size. Second, our study population is well-designed and reproducible, with standardized diagnostic criteria and failure of a first-line standardized rehabilitation plan. Third, the multicenter design allows for better reproducibility of patient selection and management, even if interventions are performed at the main study center by a single investigator. This is, however, a study strength, as it will avoid bias related to the intervention techniques.

A sham lipoaspiration procedure with the patient awake is performed to maintain blinding in the control group. Despite all precautions taken to uphold allocation concealment, breaches may occur if the patient diligently questions the procedure. For ethical reasons, if at 6 months, the progression is unsatisfactory, the intervention's nature may be disclosed if deemed clinically relevant, allowing the patient to benefit from SVF infiltration. Consequently, the study may be limited, as the initial 12-month secondary outcomes will not be considered in the final analysis. Finally, the patient selection, clinical follow-up, and rehabilitation plan might differ across the various recruitment centers (multicenter design).

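### A single published block size of 4, with the randomization done by the unblinded interventionist, makes upcoming allocations partly predictable to the one person who knows the earlier ones

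*Protocol article*

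**What the plan says.** The Randomization and Blinding section fixes four things.

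- **Ratio:** "Study participants will be randomized at a 1:1 ratio".
- **Tool and block size:** "using a randomization table and blocked randomization with blocks of 4 patients". One size is given, and it is public.
- **Strata:** age split at 40 years, and three grades of cartilage defect. No other stratification factor is named.
- **Who randomizes and when:** "The unblinded investigator responsible for the study interventions will perform the randomization shortly before administering the interventions". The only limit stated for the unblinded investigator who prepares the injectate is that this person "will be unblinded and will not participate in outcome assessments".

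Three other places bear on the point. Study Setting says "All the interventions will be performed in the lead center". The Discussion says that "interventions are performed at the main study center by a single investigator". Eligibility Criteria says "Informed consent will be obtained by the local site investigator", without saying whether that person can also be the unblinded investigator.

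Table 1 puts consent and eligibility at screening and randomization at baseline. A footnote allows both visits on one day.

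**The concern.** The person who draws the allocation is the one who carries out the real or sham harvest. By role, this person knows which arm earlier patients received. Permuted blocks force balance at the end of each block, so knowledge of the earlier draws is information about the next one, and more so when the block is short and its size is known.

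The exposure is the next open slot in a stratum before the next patient is enrolled, scheduled and graded. If someone who can predict that slot also has a say in who comes next, or in how a borderline defect is graded, the arms may differ in prognosis for reasons other than chance. Adjustment can deal with imbalance in measured baseline variables. It cannot deal with selection on features that were not recorded.

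The point does not rest on what the article leaves out. The article itself states the actor, the tool and the block size.

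**Working it through.** **Inputs.** Ratio 1:1, block size 4, and 2 age classes × 3 defect grades = 6 strata (Randomization and Blinding). Total 108 patients (Sample Size). The article gives no figure for predictability, so there is none to reproduce.

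**Assumptions.** The guesser knows every earlier allocation in the stratum and always names the arm with more places left in the block, guessing at random when the two are equal.

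**One block of 4.** There are 4!/(2!·2!) = 6 equally likely sequences.

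| Position | Probability that it is certain | Probability of a correct guess |
|---|---|---|
| 1 | 0 | 1/2 |
| 2 | 0 | 2/3 (two of the three places left belong to the other arm) |
| 3 | 1/3 (the first two were alike) | 1/3 × 1 + 2/3 × 1/2 = 2/3 |
| 4 | 1 | 1 |
| Sum | 1.333 | 2.833 |

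- Certain: 1.333/4 = 33.3%.
- Guessed correctly: 2.833/4 = 70.8%, against 50% by chance.

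**Whole trial, all blocks full.** 108/4 = 27 blocks. Certain: 27 × 1.333 = 36 allocations. Correct guesses: 27 × 2.833 = 76.5.

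**Whole trial, assumed even split.** 108/6 = 18 per stratum, which is four full blocks and two patients of a fifth.

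- Certain: 6 × (4 × 1.333 + 0) = 32, and 32/108 = 29.6%.
- Correct guesses: 6 × (4 × 2.833 + 1/2 + 2/3) = 75, and 75/108 = 69.4%.

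An unfinished block lacks its last and most predictable places, so 33.3% and 70.8% are upper bounds on the expected shares, whatever the split between strata.

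**Other block designs**

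| Design | Certain | Guessed correctly |
|---|---|---|
| Fixed 4 | 33.3% | 70.8% |
| Fixed 6 | 25% | 68.3% |
| Fixed 8 | 20% | 66.6% |
| Random 4/6, undisclosed | few | about 68% |
| Random 4/6/8, undisclosed | few | about 67% |

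The fixed designs were enumerated exactly for complete blocks. The random designs, whose sizes are assumed for illustration, were simulated with 18 patients per stratum, so their comparator is the 69.4% for fixed blocks of 4. Varying the size takes away most of the certainty, because the end of a block is no longer known. The guess rate hardly moves, because naming the arm that is behind remains a good strategy.

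**The case against.** The strongest reply is that the article says little about custody of the table, and that a condensed article may leave this to the full protocol. A reader might infer that the unblinded investigator can see the next entry, so that all upcoming allocations are known. The text does not support that. Performing the randomization is compatible with opening an envelope or requesting a code, and nothing says that the table lies open. This part of the reply stands. The Discussion does mention precautions for allocation concealment, but that sentence concerns patients finding out their treatment. The drape, sham harvest and opaque syringe hide treatment after assignment and do not protect the upcoming sequence.

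A second reply is that consent and eligibility precede a patient's own draw, that age cannot be steered, and that the defect grade can be read from an MRI which inclusion already requires. For that patient the late draw is protective, and this also stands. It does not cover the next slot in the stratum, which can be predicted before the next patient is classified.

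A reader might also infer that patient order or stratum will be steered, or that the blinded injector could follow the sequence from syringe volume. The first needs influence over enrolment, scheduling or grading, which is neither stated nor excluded. The second is a separate blinding question, and nothing says that the injector selects patients.

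Finally, the Discussion's single operator may not be the unblinded investigator, since the Interventions section gives the injection to a blinded one. The randomization section does speak of the unblinded investigator in the singular. If several people shared that role, each might know less.

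**Conclusion.** The point holds as a matter of partial predictability. The stated procedure gives the randomizing investigator, from past allocations alone, certainty about at most 33.3% of allocations and a correct guess for at most 70.8%. Under an even split over 6 strata this is about 29.6% (32 of 108) and 69.4%.

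The figures assume that one person fills the unblinded role throughout and keeps track of earlier allocations by stratum. Bias in selection needs one further condition, that this person affects who is enrolled, when, or in which defect grade. The article leaves that open, so this is an avoidable exposure and not a demonstrated bias. Full foreknowledge of the sequence is not shown.

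The change is still worth making, because it replaces a stated procedure with a less predictable one at little cost. The Results section describes the protocol as ready to go to the regulators, so it can still be amended.

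**What to change.** 1. **Custody and release (main remedy).** Have the list generated and held by someone outside the treating and assessing team. Release one allocation at a time, through a module in the electronic case report form or sequentially numbered opaque sealed envelopes, only after eligibility and stratum have been recorded and locked. The unblinded investigator then only receives the allocation.
2. **Block sizes.** Replace the fixed size of 4 with randomly varied sizes, and keep them in a document that site staff do not see. This removes most of the certainty. It lowers the guess rate only to about 67–68%, so it supplements the first step and does not replace it.
3. **Text.** Amend the Randomization and Blinding section accordingly. State whether the unblinded investigator takes any part in enrolment, scheduling or defect grading.

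The cost is a one-off set-up of the module or envelopes, and a slightly larger possible imbalance between the arms at the end of the trial. The sample size does not change.
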